## Abstract

Substance use disorders (SUDs), including Alcohol Use Disorder, are pressing global public health problems. Executive functions (EFs) are prominently featured in mechanistic models of addiction. However, significant gaps remain in our understanding of EFs in SUDs, including the dimensional relationships of EFs to underlying neural circuits, molecular biomarkers, disorder heterogeneity, and functional ability. Transforming health outcomes for people with SUDs requires an integration of clinical, biomedical, preclinical, and health services research. Through such interdisciplinary research, we can develop policies and interventions that align with biopsychosocial models of addiction, addressing the complex cognitive concerns of people with SUDs in a more holistic and effective way. Here, we introduce the design and procedures underlying Cognitive Dysfunction in the Addictions (CDiA), an integrative research program, which aims to fill these knowledge gaps and facilitate research discoveries to enhance treatments for people living with SUDs. The CDiA Program comprises seven interdisciplinary projects that aim to evaluate the central thesis that EF has a crucial role in functional outcomes in SUDs. The projects draw on a diverse sample of adults aged 18-60 (target *N*=400) seeking treatment for SUD, who are followed over one year to identify specific EF domains most associated with improved functioning. Projects 1-3 investigate SUD symptoms, brain circuits, and blood biomarkers and their associations with key EF domains (inhibition, working memory, and set-shifting) and functional outcomes (disability, quality of life). Projects 4 and 5 evaluate interventions for SUDs and their impacts on EF: a clinical trial of repetitive transcranial magnetic stimulation and a preclinical study of potential new pharmacological treatments in rodents. Project 6 links EF to healthcare utilization and is supplemented with a qualitative investigation of EF-related barriers to treatment engagement. Project 7 uses whole-person modeling to integrate the multi-modal data generated across projects, applying clustering and deep learning methods to identify patient subtypes and drive future cross-disciplinary initiatives. The CDiA Program will bring scientific domains together to uncover novel ways in which EFs are linked to SUD severity and functional recovery, and facilitate future discoveries to improve health outcomes in individuals living with SUDs.

## Background

Substance use disorders (SUDs)^1^, including alcohol use disorder (AUD), affect 162 million people worldwide and are associated with substantial morbidity, mortality, and disability (1–4). The socioeconomic and health impacts associated with the use of alcohol, cannabis, and illicit drugs, substantially contribute to the global burden in years living with a disability and lost to premature death (5, 6). In 2020, the World Health Organization heightened their calls for enhanced actions to curb the harmful effects of alcohol use, underscoring the global public health priority of the damaging consequences of alcohol use (7). In the US, 140,000 people die annually from excessive alcohol consumption (i.e., consuming more than 25 grams of ethanol per day) and another 70,000 from drug-related causes, costing the U.S. economy 191.6 billion dollars related to alcohol and 151.4 billion dollars due to use of other substances (8–10). Similarly, in Canada, alcohol and drug use causes almost 20,000 deaths, and costs the Canadian economy nearly 40 billion dollars annually (3). Treatments for SUDs have evidence supporting their efficacy but their availability is limited, highlighting the critical need to increase access to treatments and develop novel and improved interventions for SUD (11).

To advance the understanding of addiction, research on the cognitive and neurobiological factors involved in the development and maintenance of SUD is crucial (12). Contemporary models underscore the centrality of cognition to different phases of SUD development, with a strong emphasis on executive functions (EF) such as response inhibition and decision-making, in conjunction with motivational (e.g., incentive salience, cue reactivity/craving) and affective (e.g., negative emotionality) factors (13, 14). While motivational and affective factors have received extensive attention in the field of SUD research [e.g (15–19)], comprehensive studies of EF and its component processes are relatively scarce, despite the proposed centrality of EF to treatment response and functional outcomes (20, 21).

Further, studies to date have most commonly used relatively “pure” or homogeneous patient groups (e.g., adults with a specific SUD and with no psychiatric comorbidities), with more limited attention to individual differences or within-group variability (22–24). Yet, adults seeking treatment for addiction represent a highly heterogeneous group, with complex substance use histories, often meeting criteria for multiple SUDs, and a high prevalence of psychiatric comorbidities (25–27). Since “pure group” studies have limited generalizability to patient populations seen in real-world clinical settings, there is a critical need to characterize heterogeneity of executive dysfunction in a large inclusive cohort study involving a complex patient population that is characteristic of large tertiary care facilities.

To fill these gaps, we introduce the protocol for the Cognitive Dysfunction in the Addictions (CDiA) program - an integrative team-science and translational research program aiming to evaluate the central thesis that EF is crucial to SUD pathophysiology and functional outcomes. The program aims to aid the discovery of shared versus uniquely affected EF domains (28, 29) across 7 interconnected projects spanning a diverse set of methodologies and perspectives.

While there is ongoing debate about the precise number of “core” processes that define EF, converging evidence suggests that EF comprises at least three factors that are related but distinct on a behavioral and neurobiological level (30–34): 1) *inhibition*, or the ability to prevent the processing of irrelevant information in working memory and/or inhibit a context-inappropriate behavioral response; 2) *working memory updating*, or the ability to monitor the contents of working memory for relevance to the current task and to remove from or add information to working memory; and 3) *set shifting*, reflecting the ability to switch between multiple operations or task sets. These processes are supported by common and dissociable neural substrates within a distributed network of frontoparietal brain regions (35), subserved by known biological and neurotransmitter systems (36, 37), and may be partially genetically influenced (38). EF “deficits” refer to impaired functioning in one or more of these domains, whereas EF “biases” reflect the specific or selective influences of motivational or emotional contexts or materials on EF performance (39).

SUDs can be associated with both deficits and biases in EF accompanied by structural and functional alterations in underlying neural circuitry (40). Problems with EF lead to functional impairment across all stages of addiction. Interventions that bolster EF may mitigate the influence of attentional and behavioral control on drug-seeking and use. For example, computerized cognitive retraining may improve working memory capacity (41–43) and reduce impulsive choice and valuation of specific rewards in addiction (44). Further, non-invasive brain stimulation has exhibited promise across a range of SUDs and appears to impact both craving and decision-making processes (45–47). However, the deficits and biases of EF most linked to functional outcomes, as well as their respective biological bases, remain to be identified and targeted for maximal therapeutic benefit.

By embedding a multilevel assessment of EF in an interdisciplinary research program, CDiA will aid the discovery of shared versus uniquely affected EF domains (28, 29) in a large heterogeneous cohort of adults seeking help for SUDs. Parallel biomarker studies in human participants and translational mechanistic studies in relevant preclinical models will link domains of EF to putative biological underpinnings, together paving the way for the rational design of targeted and individualized therapeutics for treatment and improving functional outcomes in SUDs. Linkages to health care administrative databases will further mobilize knowledge to help shape public health policy and effect change at the societal level.

CDiA consists of seven interconnected projects (P1-7) with the following main objectives, each designed to evaluate and elaborate on the Program’s central tenet that EF is crucial to SUD functional outcomes:

To identify domains of EF linked to functional outcomes in adults seeking treatment for SUD (Project 1).To identify imaging biomarkers (MRI, fMRI) associated with domains of EF and those most predictive of functional outcomes in adult outpatients seeking treatment for SUD (Project 2).To identify biomarkers mechanistically associated with EF and functional outcomes in adult outpatients seeking treatment for SUD (Project 3).To assess the impact of repetitive transcranial magnetic stimulation (rTMS) on EF deficits in adult outpatients seeking treatment for comorbid AUD and major depressive disorder (Project 4).To study the impact of alcohol on EF deficits, and their reversal by novel therapeutic interventions, in a preclinical animal model (Project 5).To assess links between EF, treatment-seeking for SUD, and healthcare utilization and costs (Project 6).To identify subtypes of individuals seeking SUD treatment using cross-disciplinary data types from all projects and map the biopsychosocial drivers of cognitive dysfunction in SUDs (Project 7).

Apart for the preclinical project (Project 5), all projects draw on a common sample of adults seeking treatment for SUD, allowing for the triangulation of evidence within the same pool of participants. Alcohol was chosen as the main substance of interest in Projects 4-5 and the qualitative component of Project 6, as those are targeted experimental/qualitative studies that necessitate smaller sample sizes with more homogeneous characteristics. This choice was also dictated by epidemiological estimates, which suggest AUD is the most common type of SUD observed in the US and Canada (48, 49). AUD is therefore also expected to be the most common diagnosis in CDiA. Once established, the proposed research platform can be used to study other types of SUD or more complex populations in the future.

The CDiA Program benefits from the full participation of a Living Expertise Research Advisory (LERA) committee, which is composed of community members who self-identify as having living or lived experience with SUD either directly or as a family member. Incorporating the perspectives of individuals with lived/living experience helps to increase the relevance and impacts of the research on the communities expected to benefit from the findings (50). In conjunction with the scientists leading the program, the LERA committee contributed to the formulation of the program and has offered ongoing insights into its public-facing materials and study procedures. The LERA committee will play a central role in interpreting the CDiA findings and sharing the results with knowledge users in the community. The CDiA Program also consults with an International Scientific Advisory Committee composed of SUD experts who provide ongoing guidance.

An overview of the CDiA Program and synergy between Projects is presented in **Figure 1**. A detailed description of each project, including the background, methods, and analytical approach, is presented below.

**Figure 1 f1:**
[figure not shown]
Overview of the CDiA research program.

## Project 1: to identify domains of EF linked to functional outcomes in adults seeking treatment for SUD

### Background

Dual Process models of addiction suggest that SUDs can result from an imbalance between a controlled process that is more intentional (for which EF are central), and an automatic process that is more implicit or involuntary (for which affective states are influential) (51, 52). EFs modulating either appetitive (desirable) or aversive (unpleasant) motivational states are compromised in those with SUDs ( (53); also see the Addiction Neuroclinical Assessment [13, 54, 55)]. Although many studies have investigated how deficits in EFs relate to outcomes among people with SUDs (56), the existing studies are often limited by small samples, very brief (3-6 month) follow up periods, narrow focus on a single substance, the absence of mental health comorbidities, and limited attention to functional outcomes (56). Further, most studies examine either EF deficits (i.e., general impairments in EF performance) or biases (i.e., EF impairments in the context of emotional or motivational material), without examining their relative importance for SUD outcomes. Thus, there is a need for integrative research incorporating all of these factors, and carefully evaluating links with both clinical and functional outcomes in a heterogeneous clinical sample followed prospectively over time.

### Objectives

The primary goals of Project 1 (P1) are to characterize EF deficits and biases and to determine which domains of EF are most predictive of functional and treatment outcomes in a complex population of adults seeking treatment for SUD to test the following hypotheses (H1a-e):

#### H1a

Deficits and biases in the three EF domains will exhibit stronger baseline associations with indicators of functioning, such as disability and quality of life, relative to other components of cognitive functioning.

#### H1b

EF deficits across all three domains will be most prominent in those with greater (i) severity and (ii) duration of SUD, whereas EF biases will be most prominent in those with concurrent mood disorders and elevated suicidality.

#### H1c

EF deficits and biases can be used to identify clusters of participants that are associated with distinct clinical features.

#### H1d

Relatively more severe EF deficits and biases at baseline will predict slower improvements in functional outcomes over and above substance use, treatment engagement, and healthcare utilization.

#### H1e

EF domains will show improvements from baseline to the one-year follow-up. Improvements in EF will be positively associated with improvements in SUD symptoms and in functional outcomes.

### Methods and planned analyses

#### Design and participants

The CDiA Program aims to recruit a total sample of 400 adults seeking treatment for AUD and/or SUD to participate in this observational, longitudinal study involving clinical and cognitive assessments at baseline and at a one-year follow-up period (see **Table 1** for a comprehensive list of clinical and cognitive assessments and the time points of each assessment). Inclusion criteria are: (1) 18 - 60 years of age; (2) meeting diagnostic criteria for a current (past year) AUD and/or SUD (not counting nicotine- or caffeine-related disorders); and (3) seeking support for substance use concerns. Exclusion criteria include: (1) acute intoxication or withdrawal; (2) active psychosis; (3) acute suicidality; and (4) history of severe head injury, dementia, severe neurodevelopmental disorders, and other medical conditions or medications that could severely impair cognition.

**Table 1 T1:** Schedule of clinical & cognitive assessments.

Procedure	Construct Measured	Baseline ^a^	Follow up ^b^	Year End ^c^
Informed Consent	N/A	✓		
Verbal confirmation of 12-hour abstinence and time of last substance use	Substance Use	✓		✓
Urinalysis and Breathalyzer	Substance Use	✓		✓
Performance-Based Measures				
CNS-Vitals ^¢ θ^	Cognitive Functioning: General	✓		✓
Iowa Gambling Task ^¢ θ^	Cognitive Functioning: Decision Making	✓		✓
Delay Discounting Task ^¢^	Cognitive Functioning: Decision Making	✓		✓
Probability Discounting Task ^¢^	Cognitive Functioning: Decision Making	✓		✓
Flanker Task ^¢ θ^	Executive Functioning: Inhibitory Control	✓		✓
N-back Task ^¢ θ^	Executive Functioning: Updating	✓		✓
Switch Task ^¢ θ^	Executive Functioning: Set Shifting	✓		✓
Interview-Based Measures				
Diagnostic Assessment Research Tool (55)^d^	AUD, SUD, and other mental health diagnoses	✓		✓
Timeline Follow Back (56)	Substance Use	✓		✓
Psychiatric Treatment History	Treatment History: Medications	✓		✓
Psychological Treatment	Treatment History: Psychological	✓		✓
Self-Report Measures				
Demographics ^$^	Identity	✓		
Bem Sex Role Inventory (Short Form) (68, 69) ^$^	Identity	✓		
Lifetime substance use history (70) ^$^	Substance Use	✓		
Alcohol Use Disorders Identification Test (71) ^$^	Substance Use and Harms	✓		✓
Drug Use Disorders Identification Test (72) ^$^	Substance Use and Harms	✓		✓
Fagerström Test for Nicotine Dependence (73) ^$^	Substance Use and Harms	✓		✓
Alcohol Use Awareness and Insight Scale (74) ^$^	Substance Use Awareness	✓		✓
Substance Use Awareness and Insight Scale (75) ^$^	Substance Use Awareness	✓		✓
Severity of Dependence Scale (76) ^$^	Substance Use and Harms	✓	✓	✓
Brief Substance Craving Scale (77) ^$^	Substance Use: Craving	✓		✓
Stages of Change Readiness and Treatment Eagerness Scale (78) ^$^	Substance Use Goals	✓		✓
Substance Use Motives Measure (79) ^$^	Substance Use: Motivation	✓		✓
WHO Disability Assessment Schedule 2.0 (80) ^$^	Functional Outcomes	✓	✓	✓
WHO Quality of life - Brief (81) ^$^	Functional Outcomes	✓	✓	✓
Patient Health Questionnaire - 9 (82) ^$^	Clinical Features: Depression	✓		✓
Generalized Anxiety Disorder - 7 (83) ^$^	Clinical Features: Anxiety	✓		✓
Childhood Trauma Questionnaire (84) ^$^	Clinical Features: Risk Factors	✓		
List of Threatening Experiences Questionnaire (85) ^$^	Clinical Features: Risk Factors	✓		✓
Coping Orientation to Problems Experienced Inventory, abbreviated (86) ^$^	Clinical Features: Risk Factors	✓		✓
Difficulties in Emotion Regulation Scale -Short Form (87) ^$^	Clinical Features: Risk Factors	✓		✓
PTSD Checklist for DSM-5 (88) ^$^	Clinical Features: PTSD	✓		✓
Wender Utah Rating Scale (89) ^$^	Clinical Features: ADHD	✓		✓
Personality Inventory for DSM – Brief Form (PID-5-BF+) (90) ^$^	Clinical Features: Personality	✓		✓
UPPS-P Impulsivity Scales - Short Form (91) ^$^	Clinical Features: Personality	✓		✓

Check marks indicate the time point at which each measure is administered.^$^self-administered with aid of research personnel.

^¢^computer-based tasks.

^θ^mandatory onsite administration.

a post-informed consent, two sessions within 1 month (360 min).

b bimonthly at months 2, 4, 6, 8, and 10, +/- 1 month; (45 min).

c two sessions to be administered at month-12, +/- 1 month (360 min).

d DART subset to assess presence/absence of the following DSM-5-TR diagnoses: Substance-related and addictive disorders (alcohol use disorder, gambling disorder, substance use disorders); Depressive disorders (major depressive disorder, persistent depressive disorder); Bipolar and related disorders (hypomanic or manic episodes, bipolar I disorder, bipolar II disorder, cyclothymic disorder); Anxiety disorders (panic disorder, agoraphobia, generalized anxiety disorder, social anxiety disorder, specific phobia); Obsessive-compulsive and related disorders (obsessive-compulsive disorder); Trauma-and-stressor related disorders (posttraumatic stress disorder); Feeding and eating disorders (anorexia nervosa, avoidant/restrictive food intake disorder, bulimia nervosa, binge eating disorder); Schizophrenia spectrum and related psychotic disorders (delusional disorder, brief psychotic disorder, schizophreniform disorder, schizophrenia, schizoaffective disorder, substance-induced psychotic disorder).

#### Measures

Interview measures will include the Diagnostic Assessment Research Tool (DART (57) to assess SUD and comorbid diagnoses, and the Timeline Follow-Back (TFLB (58) to characterize alcohol and substance use over the past 60 days. Self-report items assessing lifetime history of alcohol and substance use will also be administered, along with measures of severity of alcohol- and substance-related harms (see **Table 1**). We will measure both (a) general EF deficits and (b) biases in these functions associated with emotional and motivational states; both neutral and emotional stimuli are used in our EF tasks. The stimuli for the EF tasks are a pool of happy, neutral, and sad faces from the Karolinska Emotional Directed Faces database (KEDF (59). Each task is administered with trial blocks with emotional stimuli (i.e., to measure EF biases) and trial blocks with neutral stimuli (i.e., to measure EF deficits). A flanker task (60–63) will be used to assess inhibition, an n-back task (64, 65) will be used to assess working memory updating, and a switch task (66) will be used to assess set-shifting.

Global cognitive function will be evaluated with the Central Nervous System Vital Signs (CNS-VS (67) computerized assessment, which has been validated for use in addiction. To minimize the impact of acute intoxication on cognition and EF, we will verbally confirm participants have not used alcohol/substances 12 hours prior to their cognitive assessment (Last Drug Use Verification Form) and administer a breathalyzer test to confirm zero blood alcohol concentration at the time of testing. We will also administer a urine drug screen and collect self-report data on time since last use of each drug to account for recency of use in the analyses. Other factors relevant to understanding substance use patterns are also assessed, including demographic factors, readiness to change, substance use motives, SUD insight, SUD treatment history, and concurrent mental health difficulties. The complete battery of measures is compiled to provide a fulsome characterization of the sample, consistent with the unique perspectives of each CDiA project and with the intended generativity of the CDiA Program for future research (see **Table 1** for a full list of measures).

### Power analysis and data analytic plan

Multiple regression will be used with the clinical, functional, and demographic factors entered as simultaneous predictors of each EF domain to test hypotheses about which factors are most strongly associated with specific EF domains (H1a and H1b).

For H1c, we will conduct latent profile analyses using domains of EF as indicators of discrete latent profiles of relative deficits and biases. We will then examine the prediction of membership in these latent profiles from substance use profiles.

For H1d, latent growth curve modeling will be used to model changes in substance use frequency, SUD severity, and functional outcomes over the follow up time points. Next, rate of change will be examined as a function of baseline EF (H1a) by regressing variability in the slopes for the growth factors on baseline EF deficits and biases. These will be included as simultaneous predictors in the model to examine the specific EF domains and biases that are most predictive of change in the clinical and functional outcomes.

For H1e, we will use a generalized linear mixed effects modelling approach. EF deficits and biases will be modelled as dependent variables and time will be entered as a within-subjects factor to determine if there is significant within-person change from baseline to one year follow up. Changes over time in SUD symptoms and functional outcomes will be modelled using the same approach, with changes in EFs included in the models as a time-varying predictor of changes in these outcomes.

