### Methods and planned analyses

#### Cross-sectional data-driven subtyping

This will involve using subject clustering algorithms to identify relatively homogeneous subgroups of patients. Primary measurements from each of P1-6 will be used as input for clustering (see **Table 4** for domain definitions). The similarity network fusion (SNF) method will then be used to combine more fine-detailed, high-dimensional input variables across multiple modalities. To address the key overarching theme of this proposal, subgroups based on EF domains (including and excluding other measures, as in P1 objectives) will be of particular interest, and will be tested for distributional differences in primary prognostic outcomes of functional recovery and sustained health. The semi-supervised association-boosted SNF (abSNF) method will be used to identify subgroups with most significance to EF performance at baseline. Internal validation of group membership will be performed using bootstrap procedures. Socio-demographic, educational, and life experiential characteristics of each subgroup will be described and placed within the context of existing cross-sectional work.

**Table 4 T4:** Summary of assessment domains and measurements across study projects.

Project	Domain (instrument/source)	Measures
1	Clinical (DART, suicidal ideation) + Substance use (TFLB, AUDIT, DUDIT, SDS)	Psychiatric diagnoses, comorbidity, suicidal ideation, childhood adversity, medication, treatment engagement
		Recent and lifetime history of (poly)substance use
		Age of onset, average yearly use, heaviest period of use
	Cognition (CNS-VS, executive function tasks, other behavioral tasks)	Global cognitive function
		Executive function (Inhibition, updating, set shifting) deficits and biases
		Risk and reward behavior
	Functional impairment and quality of life (WHOQOL-BREF, WHODAS)	Physical, psychological, social, and environmental
		Cognition, mobility, self-care, getting along, life activities, and participation
2	Neuroimaging (3T MRI)	Task-based and resting state fMRI
		T1-weighted structural MRI
		Neuromelanin-sensitive MRI of SN/VTA and LC
		Diffusion MRI
3	Genomics	Assay-based genome-wide genotypes
		Assay-based genome-wide methylation profiles
	Plasma biomarkers	Inflammasome proteins (NF-KB, ERK, and p38MAPK, NALP3)
		Pro-inflammatory cytokines (IL-1β, IL-18, and ProCaspase-1)
4	Intervention (4 week TMS) clinical outcomes	Suicidal ideation (SSI)
		Depressive symptoms (HRSD-17)

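### The regression assigned to H1a contains no non-EF cognitive measure, so it cannot show whether EF relates to functioning more strongly than other cognition does

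*Protocol article*

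**What the plan says.** According to H1a, EF performance, whether scored as a deficit or as a bias, "will exhibit stronger baseline associations with indicators of functioning, such as disability and quality of life, relative to other components of cognitive functioning". The next hypothesis, H1b, asks a different question, about who shows the deficits: "EF deficits across all three domains will be most prominent in those with greater (i) severity and (ii) duration of SUD"; its second half concerns EF biases in people with mood disorder and suicidality.

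The Project 1 section on power and data analysis gives both hypotheses one model: "Multiple regression will be used with the clinical, functional, and demographic factors entered as simultaneous predictors of each EF domain". Its declared purpose is "to test hypotheses about which factors are most strongly associated with specific EF domains (H1a and H1b").

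Measures that could serve as a comparator are scheduled. The Measures section says: "Global cognitive function will be evaluated with the Central Nervous System Vital Signs". Table 1 places CNS-VS and three decision-making tasks (Iowa Gambling, Delay Discounting, Probability Discounting) at baseline, all under a cognitive-functioning label. Table 4 treats "Cognition (CNS-VS, executive function tasks, other behavioral tasks") as one domain and "Functional impairment and quality of life (WHOQOL-BREF, WHODAS") as another.

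**The concern.** A claim that one association is stronger than another needs both associations to be estimated. For H1a, three quantities must meet in one analysis: functioning, EF and non-EF cognition. The named model has only the first two. It ranks the correlates of EF, which is H1b's question.

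The practical risk is in reporting. A significant functioning coefficient in this model could be presented as support for H1a although it cannot discriminate between H1a and its opposite. If the comparison is instead devised after the data are seen, the choice of comparator scores and of contrast is open to selection.

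**Working it through.** The article states no power, sample-size or effect-size figure for Project 1, so there is no figure to reproduce. The check sets the hypothesis against the terms of the model and then illustrates the result numerically.

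**1. Terms needed against terms present.** Write F for functioning, EF for an executive-function score and C for a non-EF cognitive score.

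| | Needed for H1a | Model named for H1a |
|---|---|---|
| F | yes | yes, as predictor |
| EF | yes | yes, as outcome |
| C | yes | absent |
| Quantity | r(F,EF) against r(F,C) | partial association of F with EF |

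**2. Do the other Project 1 analyses fill the gap?**
- H1c builds latent profiles from the EF domains.
- H1d regresses growth slopes on baseline EF deficits and biases. Its paragraph cross-refers to H1a, but its outcome is a rate of change and it names no non-EF cognition.
- H1e models change in EF, and change in symptoms and functioning with EF change as predictor.

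None compares EF with other cognition.

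**3. Numerical illustration.** Inputs: N=400, the article's recruitment target ("The CDiA Program aims to recruit a total sample of 400 adults"). The documents give no correlations, so these are assumptions: r(F,EF)=0.30; r(EF,C)=0.50; r(F,C)=0.10 (H1a true), 0.30 (equal) or 0.45 (reversed). There were 4,000 replicates per scenario, two-sided level 0.05, critical value 1.966.

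*Model as written:* EF regressed on F plus two independent stand-in covariates. With standardised variables the expected coefficient of F is r(F,EF)=0.30, and r(F,C) does not enter. The expected t is about 0.30·√396/√(1−0.30²) = 5.97/0.954 = 6.26.

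*Contrast with the comparator:* Williams' test of dependent correlations,

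t = (r_F,EF − r_F,C)·√{ (N−1)(1+r_EF,C) / [ 2·(N−1)/(N−3)·D + m²(1−r_EF,C)³ ] },

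where D = 1 − r_F,EF² − r_F,C² − r_EF,C² + 2·r_F,EF·r_F,C·r_EF,C and m is the mean of r_F,EF and r_F,C.

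Hand check for r(F,C)=0.10:
- D = 1 − 0.09 − 0.01 − 0.25 + 0.03 = 0.68 and m = 0.20.
- Denominator = 2·(399/397)·0.68 + 0.04·0.125 = 1.367 + 0.005 = 1.372.
- t = 0.20·√(399·1.5/1.372) = 0.20·20.9 = 4.18.

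A t of 4.18 against 1.966 implies detection in nearly 99% of samples, in line with the simulation.

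| r(F,C) | H1a | Mean F coefficient, model as written | Significant | Contrast finds EF stronger |
|---|---|---|---|---|
| 0.10 | true | 0.299 | 100% | 98.5% |
| 0.30 | null | 0.301 | 100% | 2.4% |
| 0.45 | reversed | 0.301 | 100% | 0% |

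**4. Does the direction matter by itself?** In one simulated data set with one covariate, regressing EF on F and F on EF gave the same t (7.174 both ways). The partial test of a single association is symmetric.

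**5. Effect on H1b of keeping functioning in the model.** Assume standardised paths a (severity to EF), b (EF to function) and c (severity to function). The adjusted severity coefficient is [a − (b+ac)(c+ab)] / [1 − (c+ab)²]. With a = −0.30:

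| b | c | Adjusted coefficient | Reduction from −0.30 |
|---|---|---|---|
| 0.40 | −0.30 | (−0.30+0.49·0.42)/(1−0.42²) = −0.114 | 62% |
| 0.40 | −0.15 | (−0.30+0.445·0.27)/(1−0.27²) = −0.194 | 35% |
| 0.40 | 0 | (−0.30+0.40·0.12)/(1−0.12²) = −0.256 | 15% |
| 0.20 | −0.10 | (−0.30+0.23·0.16)/(1−0.16²) = −0.270 | 10% |

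**The case against.** The best defence is that a journal article condenses its analysis plan. The predictor list is visibly incomplete: the Limitations section promises that every analysis will control for recency of use, yet the Project 1 model does not list it. This weakens any inference that unlisted variables are excluded. It does not supply the missing comparison. Even if cognition were added, or read into the functional factors, EF would still be the outcome, and the model would estimate how cognition relates to EF rather than to disability or quality of life. Nor is the article silent on H1a in a way an analysis plan could simply fill: it names a model whose stated purpose is another question.

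Three stronger readings are tempting, and the documents do not support them.

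- *That having EF as outcome is itself fatal.* It is not, because the test of a single EF-functioning association is the same in either direction.
- *That H1b is biased by adjusting for functioning.* H1b and the model's purpose are both worded as associations, and a mutually adjusted coefficient is a legitimate answer. It is biased only against a causal total effect that the article never states. The attenuation runs from about 10% to 60% in the cases computed, all on assumed paths.
- *That the programme's central claim goes untested.* The thesis in the Abstract is that EF matters for functional outcomes, not that it outperforms other cognition. H1d and H1e address that thesis with functioning as outcome.

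The choice of comparator also needs care. The article's opening Background section gives decision-making as an example of an executive function, while Table 1 labels those tasks as cognitive functioning. CNS-VS is described only as global, so its scores cannot all be assumed free of EF content.

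**Conclusion.** The concern holds for H1a. Run as written, the named regression yields no estimate of the hypothesised difference and can neither support nor refute it. That follows from the terms in the model and does not depend on the simulated correlations, which are assumptions used only to show the consequence: the same coefficient of about 0.30 whether H1a is true, null or reversed. The defect is the absent comparator. It is confined to one observational hypothesis of Project 1; H1b, H1d and H1e are not invalidated by it.

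**What to change.** For H1a, replace the shared model with one that has functioning as outcome:

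- Model WHODAS 2.0 and WHOQOL-BREF separately on standardised EF deficit and bias scores together with standardised non-EF cognitive scores, adjusting for demographics and recency of use. Code all scores in the same direction.
- State the contrast in advance: a difference in coefficients, incremental R-squared of the EF and non-EF blocks with a bootstrap confidence interval, or a test of dependent correlations.
- Use CNS-VS scores that lie outside the three EF domains as the main comparator, and list them beforehand.
- Declare in advance whether the decision-making tasks count as EF, or confine them to a sensitivity analysis.

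Keep the present regression for H1b. Reporting H1b with and without the functional measures is an optional sensitivity analysis.

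The cost is a few sentences of analysis-plan wording. No new measure, visit or participant is needed.
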